**Methods:**

A total of 68 participants will be recruited and allocated to 2 groups matched in age and gender, with consideration given to the preferences of participants and their guardians. The control group will receive standard in-hospital medical treatment and health education, whereas the experimental group will receive a 6-month digital therapy–based aerobic exercise intervention in addition to standard care. Outcomes will be assessed at baseline and 3 and 6 months, with data collected for analysis. The primary outcomes are the 6-minute walk distance and the timed scores (in seconds) for the timed up and go and stair climb tests. The secondary outcomes include body composition, grip strength, and quality of life measured using the Pediatric Quality of Life Inventory version 4.0.

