### Control Group Program

Children with neuroblastoma who meet the inclusion criteria will be introduced to the study’s purpose. After obtaining informed consent, a baseline survey will be conducted using a self-developed questionnaire that includes demographic and disease information extracted from the hospital’s information system. Additional baseline measurements include height, weight, BMI, 6MWD, body composition, grip strength, and PedsQL 4.0 score. The control group will receive standard in-hospital medical treatment and health education. At the 3- and 6-month follow-up visits, outcome assessments and questionnaires are administered to the control group (demographic and baseline disease information are not collected).

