### Withdrawal Criteria

Participants will be withdrawn from the study for the following reasons: (1) serious violation of the test protocol by the participant or their guardian or (2) receipt of other treatments by the participants during the trial that interfere with the study.

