### Suspension Criteria

This study will be suspended or terminated for participants under the following circumstances: (1) failure to complete the 6-month intervention as required by the study protocol, (2) occurrence of serious safety issues that compromise participant safety, (3) significant protocol deviations that hinder efficacy or safety evaluation, (4) a decision by the ethics committee to suspend or discontinue the study, or (5) a decision by the study sponsor to suspend or halt the study.

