### Statistical Analysis

Data will be analyzed using SPSS (version 26.0; IBM Corp). Primary models using the intention-to-treat principle will be conducted for all primary and secondary outcomes. Data normality will be assessed initially. Nonnormally distributed data will be presented as medians with IQRs. Between-group comparisons (intervention vs control) for these variables will be conducted using the Mann-Whitney *U* test. Within-group comparisons (baseline vs each follow-up) will be conducted using the Wilcoxon signed rank test. Categorical data will be reported as numbers with percentages and analyzed using the chi-square test. Differences in primary and secondary outcomes between the intervention and control groups across all assessment time points will be evaluated using mixed-model analysis. Statistical significance will be defined as a *P* value of <.05, with multiple comparisons adjusted using the Bonferroni method.

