### Sample Size Calculation

The sample size was calculated using G*Power (version 3.1.9.7; Heinrich Heine University Düsseldorf). On the basis of a related study [32], an effect size of 0.953 was determined, derived from the difference in the 6MWD between the experimental group (mean 35.89, SD 8.46 laps) and the control group (mean 26.76, SD 10.57 laps) after the intervention. The significance level (α) was set at .05, and the power (1 – β) was set at 0.95. The calculation indicated that 30 participants were required for each group. To account for a potential 10% loss to follow-up, 34 participants per group were planned for recruitment, resulting in a total sample size of 68 participants.

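### Ending the study for children who do not complete the 6-month intervention conflicts with intention to treat and, by inference, leaves month-6 outcomes missing in the exercise arm only

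*Protocol article*

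**What the plan says.** The Suspension Criteria open with "This study will be suspended or terminated for participants under the following circumstances", and the first circumstance listed is "failure to complete the 6-month intervention as required by the study protocol". The Withdrawal Criteria also take a participant out of the study for serious violation of the protocol or for "receipt of other treatments by the participants during the trial that interfere with the study". Neither section says that a child removed in this way is still assessed at 3 and 6 months.

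The Statistical Analysis section states: "Primary models using the intention-to-treat principle will be conducted for all primary and secondary outcomes". It adds that the groups will be compared across all time points with a mixed model and that multiple comparisons will be Bonferroni-adjusted.

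On the arms, the Abstract (Methods) says that "the experimental group will receive a 6-month digital therapy–based aerobic exercise intervention in addition to standard care". For controls, Control Group Program says: "The control group will receive standard in-hospital medical treatment and health education". It continues: "At the 3- and 6-month follow-up visits, outcome assessments and questionnaires are administered to the control group".

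Two other sections bear on the point. Compliance Supervision sets an 80% adherence threshold for platform log-ins and has the researchers contact children below it to record the reasons. Sample Size Calculation raises 30 per group to 34 with the words "To account for a potential 10% loss to follow-up".

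**The concern.** An intention-to-treat comparison at month 6 needs month-6 results from the children allocated, including those who stopped the programme. A rule that ends the study for those children stops the results from being collected. The Statistical Analysis section then promises something that the Suspension Criteria prevent.

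The rule is also unlikely to act evenly. Controls have no 6-month programme that they could fail to complete. Outcomes would go missing in one arm, for a reason tied to the intervention. Children who give up a fatigue-graded exercise programme plausibly walk less far and move more slowly than those who finish. If so, the children left in the exercise arm are a favourable selection, and the three primary outcomes shift towards the intervention without any true effect.

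**Working it through.** **Step 1. Does the text end follow-up, or only the programme?** Adverse Events, and the last sentence of Quality Control and Quality Assurance, speak of discontinuing or suspending the intervention. The Withdrawal Criteria speak of leaving the study, and the Suspension Criteria of the study itself ending for participants. The article therefore has wording for stopping the programme alone and does not use it for non-completion. Nothing in the Suspension Criteria or in Table 2 keeps such a child for the week 12 or week 24 visit.

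**Step 2. On which arm can the criterion act?** The Suspension Criteria name no arm. The Abstract, Experimental Intervention Program and Control Group Program give a 24-week programme to the experimental group only. So this one criterion has nothing to act on among controls. That is an inference from the design, not a statement in the text.

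**Step 3. The plan's own sample size.** Inputs from Sample Size Calculation: means 35.89 and 26.76 laps, SDs 8.46 and 10.57, alpha .05, power 0.95.

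- Effect size: (35.89 − 26.76) / √((8.46² + 10.57²)/2) = 9.13 / 9.573 = 0.954 (stated 0.953).
- Two-sample t test, two-sided (sidedness is not stated, but two-sided gives the stated number): 30 per group, power 0.952.
- Allowance for 10% loss: 30 / 0.9 = 33.3, rounded up to 34; 68 in total.

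The stated figures reproduce. The point here does not change them.

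**Step 4. Power with the rule in place.** Assumptions: effect 0.953, 34 allocated per arm, 31 controls retained (34 × 0.9 = 30.6), all losses in the exercise arm counted within the removed share.

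| Removed from exercise arm | Left | Power |
|---|---|---|
| 10% | 31 | 0.958 |
| 20% | 27 | 0.945 |
| 30% | 24 | 0.931 |
| 40% | 20 | 0.903 |

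The power loss is modest. Selection is the issue.

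**Step 5. Bias with no true effect.** The documents give neither a non-completion rate nor an outcome difference between completers and non-completers, so both are assumed. The analysis illustrated is an unadjusted comparison of those remaining at month 6, two-sided .05, 31 controls. Outcomes are scaled so that higher is better.

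*Model A: fixed gap.* Bias = share removed × (completer mean − non-completer mean). With 30% removed (24 left):

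- gap 0.5 SD: 0.3 × 0.5 = 0.15 SD, rejection 8.4%
- gap 1 SD: 0.3 × 1 = 0.30 SD, rejection 19.2%

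*Model B: completion correlated with outcome.* Bias = ρ × φ(z_q) / (1 − q), where q is the share removed, z_q the normal quantile at q, φ the normal density, and ρ the assumed correlation, 0.3 or 0.5. At q = 0.10: φ/(1 − q) = 0.1755/0.9 = 0.195, so the bias is 0.3 × 0.195 = 0.058 to 0.5 × 0.195 = 0.097 SD. Rejection rates are from 20,000 simulated trials.

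| Removed | Bias (SD), ρ = 0.3 to 0.5 | Rejection |
|---|---|---|
| 10% | 0.06 to 0.10 | 5.5% to 6.4% |
| 20% | 0.11 to 0.18 | 6.5% to 10.1% |
| 30% | 0.15 to 0.25 | 8.2% to 14.2% |

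Across both models and 10% to 30% removed, the bias runs from about 0.06 to 0.30 SD and rejection from about 5.5% to 19%.

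**Step 6. Bonferroni.** If the adjustment covers the three primary outcomes (an assumption), alpha is .05/3 = .0167. The Model A rates at 30% removed become 3.3% and 9.4% per outcome, against a nominal 1.67%. The bias itself does not change.

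**The case against.** The Suspension Criteria are loosely written. They mix events in one child with decisions about the whole trial, and the first item may only describe dropouts. A condensed article may also leave retention after stopping to the full protocol. The second half of this carries little weight: the objection is not to an omitted detail but to a printed rule that runs against the printed analysis principle. If the sponsor means something milder, the text still has to say so.

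The other side is right on several stronger readings that a reader might infer:

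- *That the rule removes non-adherers.* Under Compliance Supervision, adherence below 80% leads only to contact. Failure to complete is not defined, so the point concerns non-completers. How the two sections relate is itself unclear.
- *That the trial becomes exercise completers against all controls.* The withdrawal rules, and the suspension items on safety and on protocol deviations, name no arm and can remove controls too. Only the non-completion item is one-sided.
- *That no analysis could help.* Nothing says that data already collected are discarded. The mixed model would use baseline and any month-3 values, which reduces bias where dropout follows observed values. It does not cure dropout that depends on the unseen month-6 state.
- *That the 10% allowance leaves these removals out.* Sample Size Calculation does not say whether they are inside or outside it.
- *That the bias is known to be large.* The figures rest on assumed rates and gaps and do not model the planned mixed model. At 10% removed the effect on the error rate is slight.

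**Conclusion.** The point stands as a contradiction between two stated rules. Read as written, the Suspension Criteria stop collection of the primary outcomes at month 6 for children who do not complete the exercise programme, and the Statistical Analysis section promises an analysis that needs those outcomes. That the loss falls on the experimental arm alone is an inference from the description of the arms, and it holds for this criterion only. That it is related to function, and so favours the intervention, is probable but not shown in the documents.

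The size is unknown because no non-completion rate is given. The illustrative range of 0.06 to 0.30 SD, with 5.5% to 19% rejection under no effect, belongs to 10% to 30% removed, an unadjusted comparison of those remaining and two-sided .05. The mixed model removes this bias only if the missing values are missing at random given what was observed. The sample size of 30 evaluable and 34 recruited per group is not in question. The point matters before recruitment because outcomes that were not collected cannot be recovered later.

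**What to change.** Reconcile Compliance Supervision, Withdrawal Criteria, Suspension Criteria and Adverse Events with Statistical Analysis by defining two separate events: discontinuation of the intervention and discontinuation of study follow-up. Then state that:

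- not completing the programme, deviating from the protocol or receiving other treatment does not by itself end follow-up;
- such children are still invited to the week 12 and week 24 assessments, where consent and safety allow;
- every child is analysed in the arm to which the child was allocated.

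Leave the suspension items on serious safety issues, ethics committee decisions and sponsor decisions as they are. A rule that only withdrawn consent or inability to attend can end follow-up would override them and is not proposed.

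The cost is a change of wording and attendance at a few more visits that Table 2 already schedules. The observed effect may be smaller, because children who stopped exercising are then counted. The sample size does not change.

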### Adverse Events

All adverse events (AEs) occurring during the trial will be documented in an AE form. Investigators will assess the relationship between AEs and the intervention and determine whether to discontinue the intervention. AEs will be followed up on until resolution.

### Comprehensive Assessment

Efficacy assessments will be conducted by qualified rehabilitation therapists at baseline and 3 and 6 months. Assessments will include (1) demographic and physical developmental indicators (height, weight, and BMI), (2) 6MWD, (3) timed up and go (TUG) test, (4) stair climb test (SCT), (5) body composition, (6) grip strength, and (7) PedsQL 4.0 score (Table 2).

**Table 2 table2:** Study timeline.

			Screening entry period: visit 0 (day 1)		Treatment period: visit 1, week 12 (–6 days to +6 days)		Treatment period: visit 2, week 24 (–6 days to +6 days)
Informed consent			✓				
Inclusion and exclusion criteria			✓				
Basics			✓				
Measurement of human body parameters			✓		✓		✓
**Instrument-based test**							
	Body composition determination	✓		✓		✓	
	Muscle power	✓		✓		✓	
**Quality of life**							
	Score on the Chinese version of the PedsQL 4.0^a^	✓		✓		✓	
**Outcome measures**							
	6-minute walk to test walking distance	✓		✓		✓	
	Timed up and go test	✓		✓		✓	
	Stair climb test	✓		✓		✓	
	Adverse event assessment	✓		✓		✓	

^a^PedsQL 4.0: Pediatric Quality of Life Inventory version 4.0.

### Primary Outcome Measure

#### 6MWD Measure

The 6-minute walk test is conducted in a flat, 30-m corridor. Participants are instructed to walk as far as possible within 6 minutes without running or jogging. The total distance walked back and forth along the corridor during the 6-minute period is recorded. The distance is measured in meters with an accuracy of 0.1 m. Vital signs, including HR (pretest resting HR and immediate posttest HR), respiratory rate, blood pressure, oxygen saturation, and the Borg subjective fatigue score, are assessed and documented both before and after the test.

For the test environment, a 30 m–long corridor with marked lines at 1-m intervals will be used, and bright-colored strips are attached to the ground to indicate the start and end point of each 60-m segment.

The test requires that participants wear comfortable, walkable shoes; avoid strenuous exercise for at least 2 hours before the test; and rest for a minimum of 10 minutes before the test begins.

If a participant experiences physical discomfort during the test, they may take a short break by leaning against the wall and resume walking once they feel better. The timer will not be paused during this process. If the test is terminated early (before 6 minutes), the following information must be recorded: (1) the time at which the test was stopped, (2) the reason for early termination, and (3) the total distance walked up to that point.

#### TUG Test

The TUG test will be used to assess functional mobility due to its reliability, cost-effectiveness, and efficiency [31]. During the test, the participants will be instructed to rise from a chair, walk a distance of 3 m, turn around, return to the chair, and sit down again. The total time taken to complete this task will be quantified in seconds. Performance is inversely related to the score, meaning that a shorter time indicates better functional mobility.

#### SCT Measurement

The SCT will be used to assess functional mobility, including domains such as strength, speed, and axial movement (rotation). The SCT requires participants to ascend a 10-step staircase, promptly turn around at the top, and descend back to the starting point. Children will be instructed to perform the task as quickly and safely as possible without pausing and are permitted to use the handrails. The total completion time, recorded in seconds, serves as the primary outcome measure, with shorter times reflecting better performance [31].

### Secondary Outcome Measures

#### Body Composition Index

A body composition analyzer (InBody 260) will be used to measure the patients’ body composition: body fat percentage, basal metabolic rate, skeletal muscle mass, waist-to-hip ratio, body water, protein, and inorganic salt content.

#### Grip Strength

Grip strength will be measured using a TKK-5401 grip strength meter produced by Takei. The participants’ body will be in an upright position, with their feet shoulder-width apart, arms naturally hanging down, and palms inward and one hand holding the grip strength meter at full grip strength. During the measurement, the assessor must ensure that the grip strength meter does not touch the participant’s body or clothing. The value displayed on the device is then recorded by the assessor. The test is performed twice (alternating hands), a 15-second break is allowed between measurements, and the best results are retained for the stronger hand, with grip strength measured in kilograms accurate to 0.1 kg.

#### Score on the PedsQL 4.0 Scale

The Chinese version of the PedsQL 4.0 scale will be used in this study. This scale has demonstrated good reliability and validity and has been widely adopted in research assessing quality of life among children in China. The PedsQL 4.0 scale comprises 23 items, which are categorized into 4 domains: physical functioning, emotional functioning, social functioning, and school functioning. Each item is rated on a 5-point Likert scale ranging from 0 to 4. During scoring, responses are transformed into a scale from 0 to 100, where higher scores indicate better outcomes. The domain score is calculated by summing the scores of all items within that domain and dividing by the number of items in the domain. Similarly, the total summary score is derived by summing the scores of all 23 items and dividing by the total number of items. Both the domain scores and the total summary score range from 0 to 100, with higher scores reflecting a better quality of life.

### Statistical Analysis

Data will be analyzed using SPSS (version 26.0; IBM Corp). Primary models using the intention-to-treat principle will be conducted for all primary and secondary outcomes. Data normality will be assessed initially. Nonnormally distributed data will be presented as medians with IQRs. Between-group comparisons (intervention vs control) for these variables will be conducted using the Mann-Whitney *U* test. Within-group comparisons (baseline vs each follow-up) will be conducted using the Wilcoxon signed rank test. Categorical data will be reported as numbers with percentages and analyzed using the chi-square test. Differences in primary and secondary outcomes between the intervention and control groups across all assessment time points will be evaluated using mixed-model analysis. Statistical significance will be defined as a *P* value of <.05, with multiple comparisons adjusted using the Bonferroni method.

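### A nonnormal primary outcome gets two unranked between-group tests, one with no stated baseline adjustment, and no main time point is named

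*Protocol article*

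**What the plan says.** All the relevant text is in the Statistical Analysis section of the protocol article, in this order:

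- A general statement: "Primary models using the intention-to-treat principle will be conducted for all primary and secondary outcomes". It does not say which procedure these models are.
- A gate: "Data normality will be assessed initially".
- For variables judged nonnormal: "Between-group comparisons (intervention vs control) for these variables will be conducted using the Mann-Whitney" U test. No visit, baseline term or covariate is mentioned.
- For the same variables: "Within-group comparisons (baseline vs each follow-up) will be conducted using the Wilcoxon signed rank test".
- For every outcome, with no normality condition: "Differences in primary and secondary outcomes between the intervention and control groups across all assessment time points will be evaluated using mixed-model analysis". No model term or visit contrast is singled out.
- A 5% significance level, "with multiple comparisons adjusted using the Bonferroni method". The set of comparisons to be adjusted is not defined.

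On timing, the Abstract says "Outcomes will be assessed at baseline and 3 and 6 months". The Comprehensive Assessment and Primary Outcome Measure sections follow the same schedule and name no main visit. Under Grouping and Masking, families with a clear preference receive the arm they prefer, and only the others are randomised. The Abstract adds that the groups are matched in age and gender.

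**The concern.** When the normality check flags a primary outcome, the same question (do the arms differ?) is answered by a rank test and by a mixed model. If the two disagree, nothing says which one decides. The visit at which they are read is also open, so the reported conclusion could be settled after the data are seen.

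The two tests also treat baseline differently. The mixed model spans all visits and so has the baseline values available to it. The rank test has no stated adjustment. In a fully randomised trial that would mainly cost precision. Here some children are allocated by preference, and those who choose an exercise programme may already be fitter. Matching on age and gender does not balance baseline walking distance, timed up and go or stair climb time. A Mann-Whitney test of follow-up values would carry any such gap into the result.

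**Working it through.** **The plan's own figure.** The Sample Size Calculation section gives 35.89 (SD 8.46) against 26.76 (SD 10.57) laps.
- Pooled SD = sqrt((8.46² + 10.57²)/2) = 9.573; d = 9.13/9.573 = 0.954 (stated 0.953).
- Two-sided two-sample t test, alpha 0.05, 30 per arm: power 0.952. The stated 30 per group reproduces, as does 30/0.90 = 33.3, rounded up to 34.
- So the sample size is sound for a t test of one post-intervention value, which is neither of the two tests in the analysis section.

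**Which tests apply to a primary outcome?**
- Judged normal: mixed model only.
- Judged nonnormal: mixed model and Mann-Whitney, unranked, each readable at 3 or 6 months.

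**Effect of a baseline gap on an unadjusted follow-up test.** Assumptions: 30 per arm, no treatment effect, a gap of b SD that persists in full to follow-up, and a two-sided 5% t test standing in for Mann-Whitney. The noncentrality is b × sqrt(30/2), with 58 degrees of freedom.
- b = 0.2: 0.2 × 3.873 = 0.775; rejection 0.119.
- b = 0.3: 0.3 × 3.873 = 1.162; rejection 0.208.

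**What baseline adjustment does.** Let r be the correlation between baseline and follow-up (assumed; the documents give none).
- Remaining variance is 1 − r². At r = 0.7 this is 0.51, a cut of 49% relative to an unadjusted follow-up comparison; 30/0.51 ≈ 59 per arm would be needed to match it unadjusted. At r = 0.5 it is 0.75, a cut of 25%.
- Remaining bias is b(1 − r). With b = 0.3 and r = 0.7 this is 0.09 SD, or 0.09/sqrt(0.51) = 0.126 residual SD, and rejection is about 7.7%. That is much lower than 20.8%, but not 5%.
- A change-from-baseline contrast (group-by-time in the mixed model) has variance factor 2(1 − r) = 0.60 at r = 0.7, against 0.51. At d = 0.953 and 30 per arm, power is 0.997 against 0.999. The gain over that contrast is small.

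**How often the two tests diverge.** This is a simulation with 4,000 runs per setting, 30 per arm, normal data and visit correlation 0.5 to 0.7. A baseline-adjusted linear comparison stands in for the mixed model.
- No effect, both tests read at 6 months: at least one is significant in 8.2% to 8.5% of trials.
- No effect, 3 or 6 months also left open: 13.6% to 14.6%.
- True effect 0.5 SD: the two disagree on significance at 6 months in 21% to 35% of trials. At 0.953 SD they disagree in about 6%.

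These are for one outcome, before any Bonferroni step. They use normal data, where Mann-Whitney should seldom be triggered, so they show only the order of size.

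**The case against.** The strongest defence is that the mixed model is evidently the main analysis. It is the only model the section names, the opening sentence speaks of primary models, and Mann-Whitney is never called primary. On that view the rank tests are simple supporting comparisons, and model terms, covariates and the visit contrast belong in an analysis plan not shown here. The nonrandomised allocation is acknowledged under Limitations, and Bonferroni is stated.

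Part of this stands. A reader might infer that the pretest chooses between Mann-Whitney and the mixed model, or that two analyses are declared primary. The text says neither: the pretest only switches the rank test on, and the mixed model runs regardless. Missing model detail alone would not be a finding. What remains is that the article itself commits to a second between-group test for nonnormal outcomes and does not subordinate it to the first. Bonferroni with no defined set of comparisons does not settle which result counts.

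A reader might also infer that the mixed model tests an overall group effect averaged over all three visits, baseline included. Under assumed correlation 0.7 that would lower power from 0.95 to 0.77, or to 0.53 with a half-size effect at 3 months. The section names no such term, and a group-by-time test is equally possible, so those figures are no part of this point. Nor does the section say that normality of raw outcomes is the check for the mixed model, and no figure in the article calls for a log scale for the timed tests.

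**Conclusion.** The point holds as an unranked overlap. A primary outcome judged nonnormal has two stated between-group tests, one data-triggered and without stated baseline adjustment, and no visit is named as decisive. It should be corrected before outcome data are seen.

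The size is conditional. The 12% to 21% rejection rate rests on an assumed persistent gap of 0.2 to 0.3 SD, on Mann-Whitney being applied to follow-up values (the section does not say whether values or changes are compared), and on a t test as proxy. The 49% variance reduction rests on an assumed correlation of 0.7 and is relative to an unadjusted follow-up comparison, not to the mixed model already planned. Baseline adjustment reduces bias from a persisting gap but does not fully remove it, and it cannot make the preference-allocated part randomised. The sample size arithmetic is unaffected.

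**What to change.** In the Statistical Analysis section:

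- Name one primary analysis for each primary outcome: a mixed model of the 3- and 6-month values with group, visit, group-by-visit, the baseline value of that outcome, age and sex.
- Fix the primary contrast as the group difference at 6 months, reported with its 95% CI.
- Remove the normality check as a trigger, and keep Mann-Whitney as a prespecified sensitivity analysis that cannot replace the primary result.
- Report within-group changes descriptively. They do not compare the arms.

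The cost is slightly more analysis specification. The baseline values are already scheduled, and no new data are needed. For 6-minute walk distance taken alone, 30 per group remains enough: simulated power for the baseline-adjusted 6-month comparison at d = 0.953 was 0.985 to 0.9995 (correlation 0.5 to 0.7), against 0.93 to 0.94 for Mann-Whitney.

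### Bonferroni is valid for the multiple comparisons but is never more powerful, and sometimes less powerful, than Holm's step-down at the same family-wise .05; a cheap improvement is available

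*Protocol article*

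**What the plan says.** The Statistical Analysis section of the protocol article states: "Statistical significance will be defined as a *P* value of <.05", and continues "with multiple comparisons adjusted using the Bonferroni method". The sentence before it says that differences in primary and secondary outcomes "between the intervention and control groups across all assessment time points will be evaluated using mixed-model analysis". The section does not say which comparisons form the Bonferroni family.

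The abstract's Methods paragraph names three primary outcomes: "The primary outcomes are the 6-minute walk distance and the timed scores (in seconds) for the timed up and go and stair climb tests". It gives no order of testing among them. It also says: "Outcomes will be assessed at baseline and 3 and 6 months". The article does not single out one follow-up time as primary.

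The Sample Size Calculation section uses the walk distance alone: "an effect size of 0.953 was determined", "The significance level (α) was set at .05" and "the power (1 – β) was set at 0.95". It arrives at 30 per group, or 34 after allowing for 10% loss. It gives no effect size for the timed up and go (TUG) or the stair climb test (SCT), and the article gives no correlation between outcomes.

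**The concern.** Bonferroni with m tests holds every test at .05/m, even after some hypotheses have been rejected. Holm relaxes the threshold after each rejection and still keeps the family-wise error at .05. Where several effects are real, Bonferroni can therefore leave some undeclared that Holm would declare.

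All three primary outcomes measure walking or mobility in the same children, so it is plausible that the intervention would move more than one of them. The trial is small, and the article lists that among its limitations. Power that comes from the testing procedure needs no extra children. At stake is how often a second or third primary outcome with a real effect is declared. The validity of the trial is not in question.

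**Working it through.** **1. Reproduce the plan's own figure.** Inputs are from the Sample Size Calculation section.

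- Pooled d = (35.89 − 26.76) / √[(8.46² + 10.57²)/2] = 0.954, against 0.953 stated.
- A two-sided two-sample t test with d = 0.953, α = .05 and 30 per group has 58 degrees of freedom and noncentrality 0.953 × √(30/2) = 3.691. Power is 0.952, and 30 is the smallest n that reaches 0.95.
- 30 / 0.90 = 33.3, which rounds up to 34 per group and 68 in total.

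The stated sample size reproduces. Changing from Bonferroni to Holm alters none of these figures.

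**2. The two procedures for a family of three.**

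- Bonferroni rejects each hypothesis whose P value is below .05/3 = .0167.
- Holm orders the P values. It compares the smallest with .05/3, the next with .05/2 = .025 and the largest with .05, and stops at the first failure.

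Two facts follow without any assumption about correlation:

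- Every Holm threshold is at least .05/3, and a P value below .0167 is always reached and rejected. Holm therefore rejects everything Bonferroni rejects.
- Holm's first step is the Bonferroni test of the smallest P value. The chance of at least one rejection is therefore identical.

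**3. Size.** Assumptions that are not in the article: the family is the three primary outcomes, each tested once between groups; the TUG and SCT effects are as listed; the correlation is as listed. There are 30 evaluable children per arm, and the tests are two-sided t tests with 58 degrees of freedom.

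Exact power for a single test at .0167 is 0.886 for d = 0.953 and 0.449 for d = 0.6. Holm has no such closed form, so it was simulated (100,000 to 200,000 trials per scenario). Each cell gives Bonferroni, then Holm.

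| Effects (6MWD, TUG, SCT) | Correlation | 6MWD | TUG and SCT, each | At least one | All three |
|---|---|---|---|---|---|
| 0.953, 0.6, 0.6 | 0.5 | 0.886, 0.898 | 0.45, 0.56 | 0.914, 0.914 | 0.28, 0.45 |
| 0.953, 0.6, 0.6 | 0.7 | 0.886, 0.891 | 0.45, 0.56 | 0.896, 0.896 | 0.32, 0.48 |
| 0.953 on all | 0.5 | 0.886, 0.935 | 0.886, 0.935 | 0.982, 0.982 | 0.75, 0.88 |
| 0.953 on all | 0.7 | 0.886, 0.929 | 0.886, 0.929 | 0.964, 0.964 | 0.78, 0.89 |
| 0.953, 0, 0 | 0.5 | 0.886, 0.887 | no effect | 0.894, 0.894 | not relevant |

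With d = 0.5 on TUG and SCT, walk-distance power goes from 0.886 to 0.906, 0.893 and 0.886 at correlations of 0, 0.5 and 0.8.

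**4. Error control.** With no effect on any outcome, the simulated family-wise error is the same under both methods: 0.050, 0.045 and 0.036 at correlations of 0, 0.5 and 0.8. With an effect on walk distance only, the chance of a false rejection on TUG or SCT at those correlations is 0.034, 0.032 and 0.028 under Bonferroni and 0.047, 0.044 and 0.036 under Holm. Holm uses more of the permitted .05 but does not exceed it.

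**The case against.** The strongest reply is that the plan contains no error. Bonferroni is valid, prespecified and simple, and no other part of the article conflicts with it. That stands: this is a gain in efficiency, not a correction.

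The second reply is that the family is not named. The adjustment clause follows directly on the mixed-model comparisons over time for primary and secondary outcomes. It could refer to time-point contrasts within each model or to a larger family. That also stands. The ordering of the two methods holds for any family, but the figures above describe this trial only if the family is the three primary outcomes.

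Several stronger readings are tempting, and the documents do not support them.

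- *Holm always gives more power.* It does not for the first rejection, where the two methods coincide, and the gain fades when TUG and SCT have little effect.
- *Power is given up for nothing.* Bonferroni has simultaneous intervals that match its decisions; Holm loses that simple match.
- *Correlation among the outcomes argues for Holm.* Holm does not use the correlation. With d = 0.953 on all three, its walk-distance gain shrinks from about 6 points at correlation 0 to about 4 at 0.8. The relevant condition is that several effects exist together.
- *The procedure alone decides whether TUG and SCT effects are declared.* At d = 0.6 the decision on each timed test differs in about 11% of trials (0.56 − 0.45); in the rest the methods agree.
- *The trial needs all three outcomes significant.* The largest gains in the table are for that event, but the article sets no such criterion.

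A reader might also see that walk-distance power is 0.886 at .05/3, below the planned 0.95. That concerns how the sample size matches the adjustment, which is a separate matter.

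**Conclusion.** The point holds as an inexpensive improvement. At the same family-wise .05 and under any dependence, Bonferroni never has more power than Holm and sometimes has less.

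If the family is the three primary outcomes with 30 evaluable children per arm, the benefit is about 11 points of power for each timed test at an assumed d = 0.6. It is about 4 to 5 points for every outcome at d = 0.953 throughout (correlation 0.5 to 0.7). For the walk distance, the only outcome the trial was sized on, it is about 1 point or less in the first case and almost nil if the timed tests show no effect. The chance of at least one significant primary outcome does not change. The TUG and SCT effects, the correlations and the family are all assumptions.

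**What to change.** In the Statistical Analysis section, replace the Bonferroni clause with wording such as: *The between-group contrasts of the three primary outcomes at [the primary time point chosen by the sponsor] will be tested with the Holm step-down procedure at a family-wise two-sided level of .05; Holm-adjusted P values will be reported.*

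The choice of primary time point is the sponsor's, since the article does not name one. It and the family should be fixed before any outcome data are seen. If a wider family is intended, the sentence should name it; Holm applies in the same way.

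The cost is one sentence. The adjustment can be done by hand from three P values: multiply the smallest by 3, the next by 2 and the largest by 1, let no adjusted value fall below the one before it, and cap at 1. No change in sample size or data collection follows.

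The one drawback is that simultaneous confidence intervals will no longer correspond one to one with the test decisions. Bonferroni intervals can still be shown, labelled as such, with a note that an interval may include zero where the Holm-adjusted P value is below .05.
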